**Secondary objectives:**

(1) To determine the differences in the serum levels of pro-inflammatory cytokines among patients on Lactobacillus sp., placebo and ACT, at 4 timelines (baseline, 8 weeks after starting intervention, 12 weeks after starting intervention, and 24 weeks after starting intervention which is 12 weeks post termination of intervention).

(2) To assess the differences in severity of depression and anxiety symptoms among patients on Lactobacillus sp., placebo and ACT via use of questionnaire, at 4 timelines (baseline, 8 weeks after starting intervention, 12 weeks after starting intervention, and 24 weeks after starting intervention which is 12 weeks post termination of intervention).

(3) To investigate the changes of EEG characteristics in patients with AD after the above related treatments, at 3 timelines (baseline, 2 weeks after starting intervention, 8 weeks after starting intervention).

(4) To assess the differences in gut microbiota profiles of patients on Lactobacillus sp., placebo and ACT via the use of fecal samples, at 3 timelines (baseline, 2 weeks after starting intervention, and 8 weeks after starting intervention).

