**Study flowchart**

**Figure 3.1. Flow chart of the study**

**Data analysis**

All data analysis will be performed using SPSS software version 25.0 (SPSS Inc, Chicago, IL, USA). Descriptive statistics for socio-demographic and clinical characteristics, CIWA-Ar, PACS, AUDIT, VAS, HAMD, and HAMA scores, ERP analysis, and serum pro-inflammatory cytokine levels will be computed. All categorical variables will be presented in frequency and percentage, while all continuous variables will be reported in mean and standard deviation or median and interquartile range, depends on normality. Differences in socio-demographic and clinical characteristics between the three groups will be computed with Pearson’s chi square test or one way ANOVA or Kruskal Wallis test.

The mean difference in the primary outcome (CIWA-Ar, PACS, AUDIT, and VAS scores) for the three randomized groups (ACT, probiotic, and palcebo groups) at each specific time point (pre-intervention, 2 weeks at completion of conventional treatment [t0], post-treatment at 8 weeks [t1], post-treatment at 12 weeks [t2], and post-treatment at 24 weeks [t3]) will be assessed using one way analysis of variance (ANOVA) followed by false discovery rate adjustment. For the main pool analysis, mixed ANOVA is used to determine the interaction between the groups (ACT, probiotic, and placebo groups) and time points (t0, t1, t2, and t3) on the primary outcome ( CIWA-Ar, PACS, AUDIT, and VAS scores; interaction = intervention × time; where time is a within-subject variable and intervention effect is a between-subject variable). The main effects of intervention in the groups and time points will be presented as estimated marginal mean and standard error of mean. The study’s primary analysis will follow the intention-to-treat (ITT) principle. The data analysis for the study’s secondary outcomes (severity of anxiety and depressive symptoms, pro-inflammatory cytokines, EEG characteristics, and fecal microbiota) will be conducted similarly to the primary outcomes’ calculation. Statistical significance will be two-tailed and set to p < 0.05.

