| IL-6 |  |  |  |  |  |  |  |  |  |  |  |
| TNF-α |  |  |  |  |  |  |  |  |  |  |  |
| Fecal microbiota level |  |  |  |  |  |  |  |  |  |  |  |

* statistical significance at p < 0.05, Pro = probiotics group, ACT = acceptance and commitment group and Con = control group

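### Cytokines and fecal microbiota inherit the rating-scale ANOVA: power is lost if cytokines are skewed, and taxa tested as relative abundances can show spurious changes after a large Lactobacillus rise

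*Protocol*

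**What the plan says.** For the primary rating scales, the Data analysis section of the protocol says that the group means at each time point "will be assessed using one way analysis of variance (ANOVA) followed by false discovery rate adjustment". It continues: "For the main pool analysis, mixed ANOVA is used to determine the interaction between the groups" and the time points. The secondary outcomes are covered by one clause: "pro-inflammatory cytokines, EEG characteristics, and fecal microbiota) will be conducted similarly to the primary outcomes".

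Distribution is mentioned in two other places in that section. Continuous variables are summarised as "mean and standard deviation or median and interquartile range, depends on normality", which is a rule for descriptive statistics. Comparison of socio-demographic and clinical characteristics uses "Pearson’s chi square test or one way ANOVA or Kruskal Wallis test". Neither provision is extended to the outcome tests.

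Secondary objective (4) is "To assess the differences in gut microbiota profiles of patients on Lactobacillus sp., placebo and ACT via the use of fecal samples", at baseline, week 2 and week 8. EEG has the same three visits. Cytokines are scheduled at baseline and weeks 8, 12 and 24. In the Expected result(s) section, Table 2 reduces the microbiota to one row, "Fecal microbiota level", under columns for pre-intervention, week 12 and week 24.

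**The concern.** The protocol states a method here and does not simply leave it for later. An ANOVA on means may suit a rating-scale total. It is a weaker choice for the two laboratory outcomes, for different reasons.

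- **Cytokines.** TNF-α, IL-1β and IL-6 are measured as concentrations. If they are right-skewed, a few high values inflate the within-group variance on the raw scale, and a proportional reduction becomes harder to detect.
- **Microbiota.** A profile has many components. Expressed as relative abundances, the shares sum to one, so a rise in the supplemented genus pushes every other share down even if nothing else in the gut has changed. Because the active product is a Lactobacillus preparation, the artefact would fall on the probiotic comparison.

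At stake are secondary objective (1), which could miss a real cytokine reduction, and secondary objective (4), which could credit the product with changes in taxa that did not change.

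**Working it through.** The plan gives no figure to reproduce on this point. It states no cytokine distribution, number of taxa, Lactobacillus share or expected rise. From the plan come three arms, 30 evaluable patients per arm (Sample size estimation), two-sided 0.05, one-way ANOVA per visit and FDR adjustment (Data analysis). Everything else below is an assumption, shown over a range.

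**Cytokines.** Assume lognormal values with standard deviation s on the log scale. One arm is halved, a log shift of ln 0.5 = −0.693. The overall F test (2 and 87 degrees of freedom) was run 20,000 times on the raw and on the log scale.

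| s | raw-scale power | log-scale power | loss, points |
|---|---|---|---|
| 0.6 | 98% | >99% | 1-2 |
| 0.8 | 79% | 94% | 15 |
| 1.0 | 49% | 78% | 29 |

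With no true difference, the raw-scale test rejected in about 4-5% of runs at these values of s, so it does not produce excess false positives.

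**Microbiota, the mechanism.** Suppose a genus with share p rises f-fold and nothing else changes. The total becomes 1 + p(f − 1), and every other share is divided by it. With p = 0.02 and variability ignored:

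- f = 3: total 1.04, other shares fall by 1 − 1/1.04 = 4%.
- f = 10: total 1.18, other shares fall by 1 − 1/1.18 = 15%.
- f = 20: total 1.38, other shares fall by 1 − 1/1.38 = 28%.

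Whether a fall of that size is flagged depends on between-person variability.

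**Microbiota, the simulation.** There were 30 genera and 30 patients per arm, and only the supplemented genus was raised, in one arm. Each genus was tested by one-way ANOVA on relative abundance. The protocol does not name the FDR procedure or its family, so Benjamini-Hochberg at 5% across genera at one visit was assumed. Realised FDR is the average proportion of flagged genera that were truly unchanged, counted as zero when none is flagged.

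| rise | log-SD 0.4 | log-SD 0.8 | log-SD 1.2 |
|---|---|---|---|
| 3-fold | near nominal | near nominal | near nominal |
| 10-fold | about 0.62 | about 0.10 | near nominal |
| 20-fold | about 0.96 | about 0.34 | near nominal |

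Near nominal means about 0.03-0.07. Repeat runs with other seeds moved the larger entries by about 0.03. For the 10-fold rise, the share of the 29 unchanged genera flagged after adjustment was about 11% (log-SD 0.4) and 0.8% (log-SD 0.8). The same tests on log-ratios, with the supplemented genus left out of the reference, gave a realised FDR of about 0.03-0.06 throughout.

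**Visits.** Set side by side, secondary objective (4) schedules stool at baseline and weeks 2 and 8, while Table 2 has microbiota columns for weeks 12 and 24. No stool is scheduled at either of those two visits.

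**The case against.** Several points on the other side carry weight.

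- **The planned FDR step counts.** Read fairly, the cross-reference carries that step over to the secondary outcomes. Before adjustment, about 32% of unchanged genera are flagged at p<0.05 for a 10-fold rise at log-SD 0.4. A reader might quote that figure, but it is not the plan as written; after adjustment it is about 11%. The adjustment reduces the number flagged without curing the bias, because the shift in the shares is real.
- **The taxon problem is conditional.** No section specifies genus-level tests, relative abundances or a sequencing method. ANOVA on one diversity index would be free of the artefact. Against that, objective (4) speaks of profiles, and the single row in Table 2 is undefined.
- **Other genera may truly change.** The test product also contains prebiotics, so a scenario with all other genera unchanged is a simplification.
- **The cytokine point is about efficiency.** Skewness is an assumption, the loss at log-SD 0.6 is trivial, and a log transformation could be read as compatible with the plan. The protocol nevertheless mentions normality only for summaries and the rank test only for patient characteristics.
- **Empty model levels.** A reader might infer that the mixed ANOVA cannot be run, because its time points (weeks 2, 8, 12 and 24) do not match the stool, EEG or cytokine visits. The documents do not support that. The natural reading is the same method at each outcome's own visits. Only the mismatch in Table 2 stands.

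The simulations cover the per-visit ANOVA; the mixed ANOVA was not simulated.

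**Conclusion.** The point holds for secondary outcomes and is worth correcting. The protocol assigns a test of means on the measured scale to cytokines and microbiota, with no alternative route.

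For cytokines the harm is lost power, from 1-2 points at log-SD 0.6 to 29 points at log-SD 1.0, if values are lognormal and one arm is halved. It is not false positives.

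For microbiota the harm arises only if taxa are tested as relative abundances and the supplemented genus rises strongly against modest between-person variability. Realised FDR is then about 0.10-0.62 for a 10-fold rise and 0.34-0.96 for a 20-fold rise, at log-SD 0.8 and 0.4 respectively. For a 3-fold rise, or at log-SD 1.2, it stays near 0.05. A reader might infer that the trial will report many falsely changed genera; the documents do not give the inputs to say so.

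The conflict between Table 2 and the stool schedule rests on no assumption.

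**What to change.** Replace the cross-reference to the primary analysis for these outcomes.

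- **Cytokines:** analyse on the log scale with baseline as covariate, and report geometric mean ratios against placebo.
- **Microbiota:** use baseline-adjusted ANCOVA on a named alpha-diversity index and PERMANOVA for the overall profile. If taxa are tested, use log-ratios with the supplemented genus left out of the reference, and keep FDR adjustment across taxa.
- **Visits:** state that each secondary outcome is analysed at its own scheduled visits, namely baseline, weeks 2 and 8 for stool and EEG, and baseline, weeks 8, 12 and 24 for cytokines. Correct the microbiota columns of Table 2 to match.

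The cost is a change of wording and a little more analysis work, possibly in other software. No patients or samples are added. The downside is that results appear as ratios and distances, which are less familiar than mean differences.

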To handle any missing data, if the missing data represent less than 5% of the study’s total collected data, they will be ignored. If the missing data represent more than 5% but less than 40% of the total collected and are assumed to be randomly missing, then multiple imputation (restricted maximum likelihood estimation) will be performed using Stata 15. However, if the missing data represent more than 40% of the total collected data or are assumed to be missing either not randomly or completely randomly, then only the collected data will be used for the study’s analysis, and the missing data will be explained as a research limitation in any publications of the study’s findings [Jakobsen et al., 2017].

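### The missing-data rule analyses collected data alone when data are judged missing not at random, and measures missingness study-wide, which undermines the ITT primary analysis

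*Protocol*

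**What the plan says.** All of this is in the protocol's Data analysis section.

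- **Analysis principle.** The study's "primary analysis will follow the intention-to-treat (ITT) principle".
- **Main model.** For the four primary scales (CIWA-Ar, PACS, AUDIT, VAS), "mixed ANOVA is used to determine the interaction between the groups" and the time points t0 to t3. One-way ANOVAs at each time point are also planned.
- **Lowest tier.** "if the missing data represent less than 5% of the study’s total collected data, they will be ignored". The mechanism plays no part here.
- **Middle tier.** This applies if the missing data lie between 5% and 40% and "are assumed to be randomly missing, then multiple imputation (restricted maximum likelihood estimation) will be performed using Stata 15".
- **Fallback tier.** This applies if missing data exceed 40% or are "assumed to be missing either not randomly or completely randomly, then only the collected data will be used". The only further step is that "the missing data will be explained as a research limitation in any publications".

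The section on sample size estimation allows for 20% dropout among 108 randomised patients, 36 per arm. The ethical considerations mention possible relapse and withdrawal in the placebo group.

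**The concern.** Four features of the rule work against the stated ITT principle, and a fifth makes one tier unclear.

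1. Data judged missing not at random are sent to an analysis of collected values alone. In that situation missingness depends on values nobody has seen, so the observed patients need not represent those randomised. A sentence about limitations does not address this.
2. The branch turns on what is assumed about the mechanism. Missing at random and missing not at random cannot be told apart from the observed data, and the protocol gives no criterion for choosing. The choice nevertheless changes the primary analysis.
3. The limits refer to the study's total data, not to a given outcome, arm and visit. Heavy loss at one important visit, or in one arm, can be diluted below 5%.
4. A conventional repeated-measures mixed ANOVA uses only patients with every visit. Ignoring missing values, or using collected data alone, then removes whole patients from the main model.
5. The middle tier names restricted maximum likelihood as if it were a form of multiple imputation. These are different methods, so the tier needs clarifying before it can be carried out.

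The outcomes are craving, withdrawal and severity scales in a condition that the protocol itself describes as prone to relapse. Dropout related to outcome is therefore foreseeable, and with it a distorted comparison of arms.

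**Working it through.** The plan states no figure that can be reproduced here, because the point concerns a rule. The checks below show how the rule behaves.

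**A. The study-wide 5% limit**

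Inputs from the protocol: 108 randomised patients, and four visits in the mixed ANOVA (t0 to t3), or five with the pre-intervention visit. I count person-visits on one scale, which is my reading of the denominator.

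- Four visits: 108 × 4 = 432. Five visits: 108 × 5 = 540.
- If 21 patients miss only week 24: 21/432 = 4.9%, or 21/540 = 3.9%. Both are below 5%, so the values are ignored. Yet 21/108 = 19% of patients lack that visit.
- The limit is tight. On four visits one more missing value gives 22/432 = 5.1%, which leaves the tier. On five visits up to 26 patients fit (26/540 = 4.8%; 26/108 = 24%).

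Other timings of the same 21 dropouts:

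| Timing | Missing person-visits | Four visits | Five visits |
| --- | --- | --- | --- |
| All miss week 24 only | 21 | 4.9% | 3.9% |
| 7 leave before each of t1, t2, t3 | 7×3 + 7×2 + 7×1 = 42 | 9.7% | 7.8% |
| All leave after t0 | 21×3 = 63 | 14.6% | 11.7% |

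Only the first row reaches the ignored tier. The other two reach the imputation tier if data are assumed missing at random, and the fallback tier otherwise.

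**B. Who is left in the analysis**

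In every row a mixed ANOVA restricted to complete cases keeps 108 − 21 = 87 patients. The one-way ANOVA at a visit loses only those missing that visit.

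**C. Illustrations of bias (inputs assumed, except where noted)**

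*Relapse example.* Assume relapse in 40% on placebo and 20% on active treatment, and that relapse adds 10 PACS points. A fraction L of relapsers is lost and nobody else. The true difference is (0.40 − 0.20) × 10 = 2.0. The relapse share among those observed is r(1 − L) / [r(1 − L) + 1 − r].

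- L = 0.6: 0.16/0.76 = 0.2105 and 0.08/0.88 = 0.0909. The difference × 10 is 1.20.
- L = 0.4: 0.24/0.84 = 0.2857 and 0.12/0.92 = 0.1304. The difference × 10 is 1.55.

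*Simulated outcome-dependent dropout.* The chance of loss rises with the outcome on a logistic scale, with assumed slopes of 1 and 2 per SD.

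- Same mechanism in both arms, 20% lost overall, no true effect: no between-arm bias.
- Same mechanism, 20% lost overall, true effect 0.87 SD (4.0/4.6, the protocol's ACT figures): the observed difference is 0.78 or 0.67 SD, an understatement of 11% to 23%. The effect itself makes dropout differ, at about 26% against 14% for slope 1.
- No true effect, with 30% lost on control and 10% on active: bias of 0.16 to 0.23 SD against the active arm. Swapping the rates reverses the sign. With 36 randomised per arm, the type I error is roughly 9% to 14% instead of 5%.

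**The case against.** Much can be said for a narrower reading, and most of it stands.

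- A reader might infer that the fallback is reserved for data missing not at random. It is not. It also covers data missing completely at random, where observed cases are unbiased, and missingness above 40%.
- A reader might infer that the planned 20% dropout would be ignored. That needs virtually all of it to fall at week 24. Evenly spread dropout exceeds 5%.
- A reader might infer that the trial result will be biased. Between-arm bias is zero in the simulated case with no true effect and the same dropout in both arms. The relapse rates, loss rates and PACS increment are not in the documents, and 10 points is a third of the 0 to 30 range implied by five items scored 0 to 6. That example shrinks a real effect and does not create a false one.
- The protocol does not call relapse the main clinical risk. It is one of several listed, and it is attached to the placebo group.
- The protocol does not say when the mechanism is judged. It withholds the allocation sequence from the research team until the database is locked and gives the analysis to uninvolved statisticians. Result-driven choice of branch is therefore not shown.
- Omission of incomplete patients is not stated in the protocol. It follows from how a repeated-measures ANOVA conventionally works, and the per-visit ANOVAs do not share it.
- Details of sensitivity analyses commonly belong in a statistical analysis plan, which is not at hand. The wording on imputation and REML may mean imputation followed by a REML model.

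These points limit the size of the concern but do not rescue the rule. The rule is written into the protocol and governs the primary analysis, so sensitivity analyses added elsewhere would leave it standing.

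**Conclusion.** The concern holds in this form. The protocol prescribes a missing-data rule that undermines its own ITT primary analysis. The rule uses collected data alone under an assumption of missing not at random, selects the branch on an assumption that the observed data cannot settle, and measures missingness over the whole study.

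On the least favourable timing, up to 21 of 108 patients (19%) on four visits fall into the ignored tier, and a conventional mixed ANOVA would then omit all of them. With dropout spread evenly the share is 9.7%, and the rule's path depends on the assumed mechanism.

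The size and direction of any bias cannot be derived from the documents. A true difference of 2.0 falling to between 1.20 and 1.55 illustrates what missing-not-at-random dropout can do under assumed rates. It does not estimate what replacing the rule would recover, because a mixed model that assumes missing at random could leave much of that bias. The joining of multiple imputation and REML is a secondary point that needs clarifying.

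**What to change.** Replace the missing-data paragraph in the Data analysis section.

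- Delete the 5% and 40% limits and the switches on mechanism.
- Make the primary analysis a REML linear mixed model on all randomised patients, analysed as randomised, whatever the amount missing. Put the baseline score among the modelled responses, so that nobody is excluded for lacking a later score. Requiring a post-baseline score would itself depart from ITT.
- State that this model assumes data missing at random.
- Always run a prespecified sensitivity analysis under missing not at random, for example delta-adjusted multiple imputation.
- Report missingness by outcome, arm and visit.
- State that REML belongs to the mixed model and not to the imputation.

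The cost is a protocol wording change and modest extra analysis work. No additional patients or visits are needed.

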**Expected result(s)**

Table 1. Socio-demographic and clinical characteristics

| Variables | VRET group | | ACT group | | Treatment-as-usual control group | |
| --- | --- | --- | --- | --- | --- | --- |
| Frequency (n) | Percentage (%) | Frequency (n) | Percentage (%) | Frequency (n) | Percentage (%) |
| Age* |  |  |  |  |  |  |
| Race:  Han Chinese  Non-Han Chinese |  |  |  |  |  |  |
| Religion:  No religion  Buddhist/Confucianist/Taoist  Other religions |  |  |  |  |  |  |
| Marital status:  Married  Single  Divorce/separated/widow/widower |  |  |  |  |  |  |
| Education:  Up to primary education or lower  Up to secondary education  Up to tertiary education |  |  |  |  |  |  |
| Employment:  Employed  Unemployed/housewife/student  Retired |  |  |  |  |  |  |
| Monthly household income:  < RMB 5000  RMB 5000 to RM 10000  > RMB 10000 |  |  |  |  |  |  |
| History of pre-existing medical illness:  Yes  No |  |  |  |  |  |  |
| History of pre-existing psychiatric illness:  Yes  No |  |  |  |  |  |  |
| History of regular medication intake:  Yes  No |  |  |  |  |  |  |
| Duration of alcohol intake* |  |  |  |  |  |  |
| Average frequency of alcohol intake in a day (times/day)* |  |  |  |  |  |  |
| Average quantity of alcohol intake in a glass (glasses/day)* |  |  |  |  |  |  |
| Last alcohol intake prior to assessment* |  |  |  |  |  |  |

* in mean and standard deviation

Table 2. Comparison of the changes in the Alcohol Use Disorders Identification Test (AUDIT), Clinical Institute Withdrawal Assessment-Alcohol, Revised (CIWA-Ar), Visual Analogue Scale (VAS), and Penn Alcohol Craving Scale (PACS), Hamilton Depression Rating Scale (HAMD), Hamilton Anxiety Rating Scale (HAMA), liver function test variables and γ-glutamyltransferase between those in the probiotics group, acceptance and commitment therapy group, and treatment-as-usual control group and across three timepoints

| **Variables** | **Time 1 (pre-intervention)** | | | **Time 2 (12 weeks)** | | | **Time 3 (24 weeks)** | | | **p-value** | **Effect size** |
| --- | --- | --- | --- | --- | --- | --- | --- | --- | --- | --- | --- |
| Pro | ACT | Con | Pro | ACT | Con | Pro | ACT | Con |  |  |
| CIWA-Ar |  |  |  |  |  |  |  |  |  |  |  |
| PACS |  |  |  |  |  |  |  |  |  |  |  |
| AUDIT |  |  |  |  |  |  |  |  |  |  |  |
| VAS |  |  |  |  |  |  |  |  |  |  |  |
| HAMD |  |  |  |  |  |  |  |  |  |  |  |
| HAMA |  |  |  |  |  |  |  |  |  |  |  |
| IL-1β |  |  |  |  |  |  |  |  |  |  |  |
| IL-6 |  |  |  |  |  |  |  |  |  |  |  |
| TNF-α |  |  |  |  |  |  |  |  |  |  |  |
| Fecal microbiota level |  |  |  |  |  |  |  |  |  |  |  |

* statistical significance at p < 0.05, Pro = probiotics group, ACT = acceptance and commitment group and Con = control group

